### Sample size

The sample size calculation was done using G*Power (version 3.1.9.7) (23) based on a previous study data. The initial sample size calculated to detect an effect size of 0.58 for a two-sided significance level of 0.05 and 80% power was 26. To account for feasibility considerations and an anticipated 20% dropout, the final sample size was set at 30 participants. Since the present study is planned as an exploratory study, this sample size is not meant to give confirmatory inference, rather this study is planned to provide preliminary data regarding the role of an Ayurvedic treatment protocol in women with reduced ovarian reserve.

Follicular fluid will be collected from 10 participants who undergo Ayurveda treatment and 10 control participants who is receiving a contemporaneous IVF stimulation protocol for performing multi-omics analysis (matched by age and baseline AMH/AFC). No formal sample size calculation was performed for the multi-omics analysis, as it is hypothesis-generating and intended for exploratory purposes. Because the 10 controls included are for exploratory multi-omics analysis only, no clinical inference will be drawn between treatment and control groups.

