### Trial settings

The participants will be screened for eligibility at Amrita fertility centre, Kochi. After baseline assessment of AMH and AFC on day 2/3 of the menstrual cycle, 30 participants who are satisfying the eligibility criteria will be recruited for the study and will be admitted for Ayurveda treatment at Amrita School of Ayurveda, Kollam for a maximum of 21 days. On discharge, participants will be dispensed with internal medicines for 1 month. Post assessment will be done at Amrita Fertility Centre on day 2/3 of their next menstrual cycle which comes after completing 1 month of internal medications. Follicular fluid will be collected on the oocyte retrieval day of their next IVF cycle for multi-omics analysis (Treatment group—10 and Control group—10). The participant timeline is detailed in Table 1. The sample collected will be then transferred to Amrita School of Biotechnology for multi omics analysis.

**Table 1 tab1:** Participant timeline.

Time point	Study period				
	Visit 0—screening visit	Visit 1—baseline visit—Day 2/3 of the first menstrual cycle	Visit 2—Day 3/4 of the first menstrual cycle	Visit 3—Day 2/3 of the third menstrual cycle	Visit 4—oocyte pick up day of next IVF cycle
Enrollment					
Eligibility screen	X	X			
Informed consent		X			
Demographic information		X			
Intervention					
Initiation of Shodhana/cleansing (for a period of 18–21 days) followed by Shamana (internal medicines) for a period of 1 month at Amrita school of Ayurveda			X		
Assessments					
Serum AMH at Amrita fertility centre				X	
Ultrasound scan for AFC at Amrita fertility centre				X	
Collection of follicular fluid at Amrita fertility centre					X
Adverse events monitoring(throughout the intervention period)			X		

AFC, antral follicle count; AMH, anti-mullerian hormone.

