### Integration of multiomics data

The transcriptomics, proteomics and metabolomics data will be processed separately. The differentially expressed genes compiled after transcriptomics analysis will be studied in detail through ingenuity pathway analysis to study the upstream regulators, signalling pathways involved. Similarly, KEGG analysis will be used to determine the biological pathways that are enriched with differentially expressed proteins and metabolites. Finally, Multi-Omics Factor Analysis (MOFA) will be performed using the MOFA2 package in the Bioconductor software package (release 3.21). For this, the multiomics data obtained will be trained and analyzed to correlate with the AMH and AFC changes at 1% FDR with BH correction. Significant genes, proteins, and metabolites will be mapped onto biological pathways or networks, and correlations with clinical outcomes (AMH/AFC changes) will be explored to highlight mechanistically relevant associations.

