## Data collection

On recruitment, participant consent will be obtained and documented in an Informed consent form (ICF) prepared in both Malayalam and English language. The basic demographic data, detailed medical history, baseline assessment details and all other relevant data will be collected and documented in an analog case report form (CRF). These will be done by the project research scientist at Amrita School of Ayurveda.

Clinical data collection: The baseline and post intervention clinical data for analysis will be collected through a blood test and ultrasound scan by experts at Amrita Fertility Centre and laboratory associated with the centre. To ensure consistency, reduces inter observer variability and improves reliability the same radiologist will perform the sonography and laboratory samples will be analysed at the same lab. To ensure quality assurance and reproducibility, standard operating procedures (SOPs) will be followed at every level of data collection and handling. Laboratory technician evaluating the biological samples and radiologist, will continue to be blind to the treatment schedules and clinical results to further enhance scientific rigour.

Follicular fluid collection: The follicular fluid will be collected from 10 participants who visit Amrita Fertility Centre after Ayurvedic treatment. Follicular fluid from 10 participants who did not avail of Ayurvedic treatment protocols undergoing IVF treatment will also be taken as control. During oocyte retrieval procedure, the follicular fluid will be aspirated from multiple follicles by the principal investigator, a Professor of Reproductive Medicine at Amrita Fertility Centre. The follicular fluid collected, after removing the cell debris through centrifugation (700 g for 10 min), will be immediately transferred to liquid nitrogen contained in the cryocan and transported to Amrita School of Biotechnology, by the project research scientist who is trained on handling and pre-processing the follicular fluid samples for performing multi-omics analysis. These samples will be transported to Amrita School of Biotechnology using a cryocan (with liquid nitrogen). Further, the follicular fluid samples will be divided into multiple aliquots in 5 mL Eppendorf tubes to avoid repeated freeze–thaw cycles and these aliquots will be stored in −80 °C till further analysis.

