Follicular fluid from 10 control participants and 10 Ayurvedic-treated participants chosen from the 30-participants treatment arm and matched according to age and baseline AMH/AFC will be obtained for the secondary, exploratory multi-omics analysis. All the laboratory experiments will be performed in triplicates (of each biological samples) and statistical analysis will be done using GraphPad Prism software. The statistical analysis of collected proteome data will be performed using Proteome Scaffold software (version 4). Peptide identifications will be accepted if they can be established at greater than 95.0% probability. The Scaffold Local FDR algorithm and peptide prophet algorithm with scaffold delta-mass correction will assign peptide probabilities. Protein identifications will be accepted if they can be established at greater than 99.0% probability and contain at least two peptides representing the protein family. The protein prophet algorithm will assign protein probabilities (34, 35). For metabolomics analysis, after data generation, the heatmaps, principal component analysis, and multivariate statistical analysis will be performed using R (Version 4.5.1) and MetaboAnalyst 6.0. To evaluate the differences between the treatment and control groups in transcriptomics, proteomics, and metabolomics, *t*-tests (for normally distributed data) or Mann–Whitney U tests (for non-normal data) will be used for each gene, protein, or metabolite. To account for multiple comparisons, the Benjamini–Hochberg FDR correction will be used; an FDR of less than 0.05 will be considered significant. As described under each section, specific assays will be used to further validate the most important genes and proteins. No formal sample size calculation was performed for the exploratory multi-omics analysis, as it is hypothesis-generating, and the 10 treatment samples were selected based on matching and feasibility.

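### The rule for choosing 10 of the 30 treated women for multi-omics does not prevent selection related to their AMH/AFC response

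*Protocol article*

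**What the plan says.** The Statistical methods section of the protocol article describes the treated omics sample as "10 Ayurvedic-treated participants chosen from the 30-participants treatment arm and matched according to age and baseline AMH/AFC". It ends by saying that no formal calculation was made for this part and that "the 10 treatment samples were selected based on matching and feasibility".

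Trial settings and Table 1 give the order of events. The response is measured at Visit 3: "Post assessment will be done at Amrita Fertility Centre on day 2/3 of their next menstrual cycle which comes after completing 1 month" of oral medicines. The fluid comes later, at Visit 4: "Follicular fluid will be collected on the oocyte retrieval day of their next IVF cycle for multi-omics analysis". Data collection adds: "The follicular fluid will be collected from 10 participants who visit Amrita Fertility Centre after Ayurvedic treatment".

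The trial is open-label. Data collection blinds the laboratory technician and the radiologist. The principal investigator, who aspirates the fluid, is not listed as blinded.

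The omics data have two uses. Treated and control samples are compared feature by feature at an FDR below 0.05 (Statistical methods). Under Integration of multiomics data, "correlations with clinical outcomes (AMH/AFC changes) will be explored". The secondary objectives look for targets and metabolites that play a part in raising AMH.

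**The concern.** Only a third of the treated arm enters the omics analysis, and the rule for choosing that third has two parts. One part, baseline matching, is fixed before treatment. The other, feasibility, is open to judgement. By the time fluid is drawn, each woman's AMH/AFC change exists and the treating team is not barred from seeing it.

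Two things could go wrong if the choice leans towards women who improved. First, the contrast with the ten controls would describe responders rather than treated women, so a feature that marks a good response could be read as an effect of treatment. Second, the correlations with AMH/AFC change would be estimated over a selected range of change.

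Baseline matching does not protect against this, because women of the same age and baseline AMH/AFC can differ in how much they change.

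**Working it through.** **The plan's own figure.** The only calculation in the plan is for the primary paired test: "effect size of 0.58 for a two-sided significance level of 0.05 and 80% power was 26". With the noncentral t distribution, power for d = 0.58 is 0.795 at n = 25 and 0.811 at n = 26, so 26 reproduces. It has no bearing on how the ten are chosen. The omics sample of 10 has no calculation to reproduce.

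**Order of events.**
1. Baseline AMH, AFC and age: Visit 1. These are the only named matching variables.
2. AMH/AFC change: Visit 3.
3. Fluid: Visit 4.
4. Choice of the ten: no time given. Even a list drawn up at baseline would be settled only by who reaches retrieval, which is after Visit 3.

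**Upper bound on enrichment.** Inputs from the protocol: 30 treated women, 10 sampled, 20% dropout (30 × 0.80 = 24). Assumption: changes are independent and normal, expressed in SDs of change. The excess is the expected mean of the 10 largest of N standard normal values, from 200,000 simulated sets:

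| Women available (N) | Excess if the 10 largest changers are taken |
|---|---|
| 30 | 1.06 SD |
| 24 (after 20% dropout) | 0.91 SD |
| 15 (assumed to reach retrieval) | 0.52 SD |

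A large-sample check for the top third: φ(0.431) ÷ (1/3) = 0.364 × 3 = 1.09, close to the 1.06 for a finite set of 30.

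**Partial selection.** If the ten are the highest on some ground that correlates ρ with change, the excess is ρ × the upper bound. The values of ρ are assumptions; the protocol gives none.
- N = 30: 0.25 × 1.06 = 0.27 SD; 0.5 × 1.06 = 0.53 SD.
- N = 24: 0.25 × 0.91 = 0.23 SD; 0.5 × 0.91 = 0.45 SD.
- Choice unrelated to change (ρ = 0): no excess.

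**Effect on the correlations.** In the extreme case (10 largest of 30), the SD of change among the ten is about 0.54 of the arm's. For an assumed true correlation of 0.6 between an omics feature and change, range restriction gives 0.6 × 0.54 ÷ √(1 − 0.36 + 0.36 × 0.54²) = 0.324 ÷ 0.863 ≈ 0.38. Simulated samples of ten average slightly lower, about 0.35.

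**The case against.** The strongest reply is that the protocol never says the ten are picked with the response in view. It dates the collection of fluid, not the choice of women, and every matching variable that it names is a baseline one. The sentence that mentions feasibility opens by explaining why there is no sample-size calculation. The Sample size section uses the word in the same way for the whole arm: "To account for feasibility considerations and an anticipated 20% dropout, the final sample size was set at 30 participants". Read so, feasibility justifies the number ten and is not a ground for picking individuals. Taking ten women who return after treatment is also compatible with consecutive sampling, and an article may leave such steps to operating procedures.

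Much of this stands. A reader might infer that responders will be chosen, or that the choice is stated to follow the response. The documents support neither: selection on response is possible, not planned. The 1.06 SD is a worst case in which matching imposes no constraint. The effect size of 0.58 is no yardstick for it, because that figure belongs to the within-subject test in all 30 women, which this choice cannot touch. Restricting the range of change would also typically weaken the correlations rather than create false ones.

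What does not stand is that this is merely missing detail. The text does state a rule, and its wording says the samples were selected on the ground of feasibility as well as matching. If only the number was meant, the sentence needs rewording anyway.

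A last fair objection is that reaching retrieval may itself depend on response, so consecutive sampling would not remove all enrichment. The protocol's Introduction supports this: it reports high cycle cancellation in these patients, and women at the centre who became eligible for treatment with their own oocytes after AMH rose. The fix therefore has to include reporting on this point.

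**Conclusion.** The concern holds in a limited form. The stated rule, the visit order and the lack of blinding beyond the technician and radiologist together allow the choice of ten treated women to be related to their AMH/AFC change. The possible excess in mean change runs from zero to about 1.06 SD out of 30, or 0.91 SD out of 24. It is about 0.27 to 0.53 SD out of 30 if the assumed correlation of the choice with change is 0.25 to 0.5. These figures assume normal, independent changes. They measure enrichment of the sample, not bias in any particular gene, protein or metabolite, which the documents give no means to quantify.

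The primary AMH/AFC analysis is not affected. The omics work is declared exploratory, and clinical inference between the groups is ruled out, so the consequence is moderate. A hypothesis-generating comparison still needs a sample whose origin can be interpreted, and this one can be secured at almost no cost.

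**What to change.** In Statistical methods, replace selection by matching and feasibility with a rule along these lines: the treated omics sample is the first 10 treated women, in enrolment order, who reach oocyte retrieval and for whom a control matched on age and baseline AMH/AFC is available; matching is done from coded baseline values, without sight of Visit 3 results.

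Because reaching retrieval may depend on response, add two reporting items: the number of treated women who did not reach retrieval, and the AMH/AFC change in sampled and unsampled treated women side by side. If feasibility was meant only to explain the number ten, say so in a separate sentence.

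The cost is a few sentences in the protocol or SAP. No extra samples, visits or staff are needed. The downside is that matches may be slightly less close than hand-picked ones.

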## Discussion

Diminished ovarian reserve characterized by reduction in oocyte quality and number often results in poor reproductive outcomes, posing a great challenge in successful assisted reproductive techniques. It was observed that DOR is the most common reason for selecting ART in fertility treatments (4). Women with DOR tend to exhibit poor ovarian response to gonadotropins, requiring higher doses of medication and prolonged stimulation protocols, yet still yielding suboptimal results. Even though various stimulation protocols (36) and other options are being tried, patients become poor responders due to low quality or quantity of oocytes. Currently, there is no established standard of care that can effectively restore the ovarian reserve, hence underscoring the need for novel and integrative treatment approaches. In recent years, traditional medicine systems like Ayurveda, Traditional Chinese medicine have attracted scientific interest for their potential in enhancing and improving various aspects thereby alleviating the disease conditions including PCOS and DOR. The importance of investigating the role and impact of traditional medicines has been highlighted through a study that used an Ayurveda treatment protocol in improving AMH values in DOR conditions (13). Another study has highlighted the importance of traditional Chinese medicine that includes herbal treatment along with acupuncture in improving the AFC and FSH levels in women with DOR (37). Similarly, the cell signalling pathways modulated in granulosa cells using Er Zhi Tian Gui Formula suggested its potential (38). The impact of few formulations including Gengnianchun and Bushen Jianpi Tiaoxue Decoction on mTOR and estrogen signaling pathways in reducing apoptosis and oxidative stress in granulosa cells has been demonstrated (39, 40). A recent meta-analysis has also shown the impact of certain East Asian interventions including herbal and acupuncture therapies in improving the live birth and clinical pregnancy rates with minimal adverse events (41). Following these approaches, this study protocol aims to investigate the feasibility and potential of an Ayurvedic treatment in improving the ovarian reserve markers in DOR patients. Through integrative approaches this study might be able to predict the advantages of traditional Ayurvedic treatment approaches in improving the ovarian reserve markers and the overall ovarian microenvironment.

### Limitations

Since this is a single-arm clinical trial, the primary objective is to explore the potential role of Ayurvedic treatment in women with DOR by assessing changes in AMH and AFC. Accordingly, the findings should be regarded as preliminary and hypothesis-generating. Also the results of this study cannot be considered conclusive or generalized without validation through larger, controlled studies. A further limitation is that the evaluation is restricted to surrogate biomarkers, namely AMH and AFC. While these provide useful information about ovarian reserve, the impact of the intervention on clinically meaningful outcomes such as oocyte quality, fertilization rate, and clinical pregnancy will not be assessed. Nevertheless, given the exploratory nature of this trial, the focus will be on generating preliminary evidence and mechanistic insights into the effects of Ayurveda-based interventions in DOR. The knowledge gained is expected to inform and guide the design of future controlled studies that will incorporate broader reproductive and clinical endpoints.

### Confidentiality

All the study related patient information and the results will be stored securely at the Amrita School of Ayurveda and Amrita School of Biotechnology. The files pertaining to the study will be securely locked in cupboards with limited access. The trial participants will be assigned a code, and this will be used for maintaining the confidentiality of the patient records and sample analysis results. None of the personnel information or identifying information will be stored along with the participant’s records. The data will be also secured in local databases with password protection.

### Dissemination plan

The clinical trial is registered in the clinical trial registry of India (crri.nic.in). The time of starting and finishing the recruitment details will be updated in the registry. After completing the data collection, the results and reports including the workflow, the demographic information of the trial participants, primary outcomes and the statistical analysis will be updated. This will be made available to the respective stakeholders including interested participants and IVF centres. The outcome of the study will be published in peer-reviewed international journals and the work will be presented in conferences and seminars. As recommended by International Committee of Medical Journal Editors, will follow all the guidelines and criteria while preparing abstracts and publications. The findings may serve as a basis for future clinical trials on Ayurvedic interventions in ART.
